**Sample size {14}**

Based on the proposed effect size from previous studies (10) and assuming a two-sided 5% significance level and a power of 80%, 35 patients will be our sample size in each group. The target sample size will be 105 critically ill COVID-19 patients, which will be allocated randomly in three trial arms with 35 patients in each group. Patients will be allocated into study groups using a simple randomization method.

**Recruitment {15}**

On each day of the study, the main internal clinical specialist will examine all newly admitted patients in each morning round and select eligible cases based on the triage, laboratory, and CT-scan findings of the patients. One of the clinical colleagues of the project will put randomly patients in three arms and explain the study plan to the patient and provides the informed consent form. The project's lead executor (the staff member responsible for study) will review the availability of all the necessary facilities and make sure that the study is done properly.

**Assignment of interventions: allocation**

**Sequence generation {16a}**

Participants will be allocated into either control or intervention groups with a 1:1:1 allocation ratio using a simple randomization method (Figure 1). We will use a computer random number generator to generate a table of random numbers for simple randomization.

**Concealment mechanism {16b}**

The project's principal investigator (PI) (unblinded member) will do the randomization procedure and check the table of random numbers. The allocation process will be concealed to the physician and researchers. Allocation concealment will be made using an opaque sealed envelope system. For this purpose, the names of the groups will be placed in opaque closed envelopes, and whenever, according to the diagnosis of the physician, one of the patients will be eligible to enter the study, one of the envelopes will be randomly selected.

**Implementation {16c}**

The PI will do the randomization procedure.The main internal clinical specialist will screen all newly admitted patients in each morning round and selected eligible COVID-19 cases. A site investigator will explain the trial for each potentially eligible patient (or their family) and ask them to participate in the study. The site investigator and two research nurses will record the data of participants into patients’ medical charts and HIS. The project's lead executor will access to the data of participants. Two blinded research nurses will follow up on the visits or phone calls. The project's lead executor will send the data to the study therapist and statistical analyzer who are not involved in the study outcome. Each datasheet form will have randomization number codes. Staff responsible for recruitment and symptom ratings is not allowed to receive information about group allocation.

**Assignment of interventions: Blinding**

**Who will be blinded {17a}**

The PI is unblinded and is responsible for the study and will handle all team. However, this person will not play a role in examining the data and interpreting the results. An unblinded researcher (a pharmacist) will cover the drug’s bottles with aluminium foil and prepare them interventions and control drugs in a syringe with a code so that patients are blinded. This person will not be in contact with patients. The staff and nurses, caring for the patients, will be unblinded for each study group due to the nature of this study. The staff that take outcome measurements will be blinded. The laboratory technicians will also be blinded as well as the statistical team. These study statisticians will have access to coded data and will analyse the data labelled as group X, group Y, and group Z.

**Procedure for unblinding if needed {17b}**

If the main coordinator suspects about an adverse event in each patient, use the emergency treatment for the patient. In this regard, the coordinator should be discussed with the main staff member if he/she believes that unblinding is necessary. All procedures for unblinding will be documented and should be reported with reason. As a final note, discontinuation of treatment will not occur after the unblinding procedure.

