**Criteria for discontinuing or modifying allocated interventions {11b}**

Participants can/will be withdrawn from the study if the patients or their families request to be excluded from the study or the study is thought to be dangerous for the patient or the risks are more than the potential benefits.

If signs of severe respiratory infections appear, treatment will be based on the doctor's opinion and the condition of each patient; as well as, the subject will be immediately withdrawn from the study. However, the patient's information will be collected in such unforeseen and adverse events and studied.

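### As written, the rule that treatment is not stopped after unblinding conflicts with the withdrawal criteria for a patient who falls under both

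*Protocol*

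**What the plan says.** Two sections of the protocol bear on what happens to a patient's treatment when harm is suspected.

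- **Procedure for unblinding if needed {17b}.** The trigger is a suspected adverse event: "If the main coordinator suspects about an adverse event in each patient, use the emergency treatment for the patient". The coordinator then discusses with the main staff member whether unblinding is needed, and the unblinding is documented with its reason. The section ends by stating that "discontinuation of treatment will not occur after the unblinding procedure".
- **Criteria for discontinuing or modifying allocated interventions {11b}.** Participants can or will be withdrawn at their own or their family's request, or when "the study is thought to be dangerous for the patient or the risks are more than the potential benefits". A second paragraph deals with signs of severe respiratory infection. Treatment then follows the doctor's judgement and "the subject will be immediately withdrawn from the study".

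A third section, **Who will be blinded {17a}**, limits how often the first two meet: "The staff and nurses, caring for the patients, will be unblinded for each study group due to the nature of this study". The section on adherence {11c} likewise says that those who prescribe the drugs know what they are.

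**The concern.** The unblinding procedure is written for patients in whom an adverse event is suspected. Some of them may also be patients for whom continuing is judged dangerous, which is the situation that {11b} addresses. For such a patient one section leads to withdrawal, and the other says that treatment will not be discontinued.

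This is a patient-safety instruction, and whoever has to act on it will have little time to work out what was intended. A rule on allocated treatment should not depend on which of two sections the reader opens first.

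**Working it through.** There is no figure to reproduce. The check sets the two sections side by side and then looks for text that reconciles them.

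**Step 1: do the sections concern the same thing?** Section {11b} speaks of withdrawal from the study, and {17b} of discontinuation of treatment. The terms differ, but the heading of {11b} is about discontinuing or modifying the allocated interventions, and its second paragraph hands treatment to the doctor. It is therefore the section that governs stopping allocated treatment.

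**Step 2: can one patient fall under both?** Yes. The trigger in {17b} is a suspected adverse event. Section {11b} covers danger to the patient and risk exceeding benefit, and its second paragraph itself classes the events it describes as adverse. Neither section excludes patients covered by the other.

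**Step 3: what does each section say in each case?**

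| Patient | {11b} | {17b}, last sentence | Compatible as written? |
| --- | --- | --- | --- |
| Not unblinded, {11b} not met | silent | silent | yes |
| Not unblinded, {11b} met | withdrawal | silent | yes |
| Unblinded, {11b} not met | silent | treatment not discontinued | yes |
| Unblinded, {11b} met | withdrawal | treatment not discontinued | no |

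Only the last row conflicts. The first paragraph of {11b} mixes a permission with a requirement (can or will). If it is a permission, {17b} removes the option; if it is a requirement, {17b} contradicts it. The second paragraph of {11b} is a plain requirement, so for that group the conflict does not depend on the looser wording.

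**Step 4: does any other section settle it?**

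- {11c} covers masking and missed doses.
- {11d} provides for daily examination of side effects and for substitute drugs, but does not say whether allocated treatment continues after a code break.
- {17a} says who is blinded.
- {21b} and {22} cover reporting and stopping the whole trial, not the individual patient.

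None makes an exception to {17b} or says which section prevails, and {11b} and {17b} do not refer to each other.

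**The case against.** The strongest reply is that the conflict depends on how one sentence is read. Two readings would remove it. The authors may have meant that unblinding alone is not a reason to stop, in which case {11b} still applies in full. Or the treatment that is not discontinued could be the emergency treatment, the only treatment named earlier in that section. Both readings are possible. Neither is what the sentence says: it is unqualified, names no particular treatment and does not mention {11b}. That two such readings are available is itself a reason to reword it.

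A second reply is that the two sections will seldom meet, since carers already know the arm and can apply {11b} without a formal code break. This stands. It lowers the likely frequency but does not reconcile the text.

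A reader might also infer more than the protocol supports:

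- **That the conflict concerns serious drug reactions in particular.** Section {17b} says only that an adverse event is suspected.
- **A number of affected patients.** This would need the share with a suspected event, the share of those formally unblinded, and the share of those who also meet {11b}. The protocol gives none of the three. Applying an assumed event rate to the intervention arms would take the last two as 100%, which is implausible when carers are already unblinded.
- **That centres will handle the same event differently.** Section {17b} gives the decision to the main coordinator in discussion with the main staff member, not to each site.
- **That code breaks will erode the blinding of patients or assessors.** Section {17b} does not say to whom the arm is revealed. Section {17a} keeps outcome staff blinded, and {16c} bars those rating symptoms from receiving the allocation.
- **That unblinded patients would be lost to follow-up or analysis.** Sections {11b} and {18b} keep collecting data after withdrawal, and {20c} specifies intention-to-treat.

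**Conclusion.** The concern holds as a contradiction in wording between {17b} and {11b}, confined to patients who are unblinded and also meet a withdrawal criterion. It rests on taking the last sentence of {17b} at face value and on reading {11b}, by its heading, as the section on stopping allocated treatment. The number of patients affected cannot be derived from the protocol and may be small.

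It should still be corrected, because both passages are stated safety rules, nothing ranks them, and the repair is simple. This conclusion takes no view on which clinical rule is right. Nor does it show that any patient would be managed wrongly, only that the protocol gives two answers for the same patient.

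**What to change.** Reconcile {17b} with {11b} so that a single section governs what happens to allocated treatment, whether or not the code has been broken. One way is to replace the last sentence of {17b} with a cross-reference to the governing section. If the intended meaning was that unblinding is not in itself a ground for discontinuation, or that the sentence concerns the emergency treatment, the protocol should say so explicitly and state how this relates to {11b}. The sponsor's clinicians decide the content of the rule.

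The cost is a one-sentence amendment, submitted by the route the protocol already sets out for amendments {25}, and a note to sites. It needs no additional patients, data or staff. No additions on follow-up, intention-to-treat or assessor blinding are needed for this point.

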**Data collection and management**

**Plans for assessment and collection of outcomes {18a}**

Several employees will daily complete all demographic and laboratory information of the patients and imported them to HIS. These persons are blinded about different study groups. The relevant patient data will be extracted via HIS and, if needed, will be completed by direct daily observation and review of patients' files by an unblinded person. The level of SpO2 (the primary outcome) will be daily measured by oximeter and the second outcomes will be extracted from HIS and evaluated. It will be assumed that all vital information of patients will be monitored continuously, as most data of patients in ICU are recorded as routine care.

**Plans to promote participant retention and complete follow-up {18b}**

All related data about the outcomes including the daily level of SpO2, vital status, intubation status, the hospital stay length, and the time of discharge will be obtained during the hospitalization, day 14, and followed up one month after the discharge time. The data will be obtained by HIS, physical visit on a bed or a telephone interview. The main coordinator will provide written feedback and send an acknowledgment to the participants or their families. Besides, all cases who withdraw their study participation will be followed one month and If they need management and health services, they will be taken care of. Moreover, information from people who have dropped out of the study will also be checked if they have received enough doses of the drugs and will not be replaced by other patients.

**Data management {19}**

All data will be entered into HIS. The system server is located in a secure data room and protected by the Golestan university firewall. Patient medical records (paper-based) will also be stored in a secure archive room and categorized with codes in numerical order. The backup files will be stored for five years. Only specific authorized people will have access to the files and access time will be recorded. The system output files will be sent as a password-protected Excel file using a flash drive for statistical review. A university VoIP (telephone) system will be set up to answer any participants’ possible questions in case of questions or problems.

**Confidentiality {27}**

The main coordinator will replace the name of each participant with a reference code in all electronically files including the password-protected Excel file. The main coordinator will store the main personal information of participants including their names and national ID numbers along with these reference codes in a secure cabinet throughout the study.

**Plans for collection, laboratory evaluation, and storage of biological specimens for genetic or molecular analysis in this trial/future use {33}**

We will not use any type of patients’ samples for future genetic or molecular analysis.

All plasma samples will be disposed of one week after the analysis due to the safety.

**Statistical methods**

**Statistical methods for primary and secondary outcomes {20a}**

All statistical analysis will be done by SPSS Statistics version 16 or will be analysed by R software. At first, the normality of variables will be checked using a Kolmogorov-Smirnov test. The continuous data with normal or skewed distribution will be analysed and showed using the number (N), mean and standard deviation (SD), or median and inter-quartile range (IQR), respectively. The frequencies and percentages will be presented for the other type of data including categorical data.

The effect of outcomes between two interventions and the control groups will be assessed by chi-square or Fisher’s exact tests for the categorical data and the independent *t*-test will be used to evaluate the normal distribution data.

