Currently, the combinations of three categories of drugs including corticosteroids, IV-IG, and interferon-beta are used experimentally by clinicians in some centers of COVID-19 patients. in this regard, some unpublished data showed some effectiveness in the improvement of cases. However, the best time to start prescribing this regimen and the best candidate for patients to use these drugs are two of the main questions that are still unclear. In a study in China in 2020, Wang et al. reported that the administration of methylprednisolone with a dosage of 1-2 mg/kg/d for 5-7 days was effective in cases with severe COVID-19 pneumonia. These cases had a faster improvement of SPO2 and shorter hospital stay days compared to the control group (10). Moreover, in another study, two doses of dexamethasone were used in infected pigs with porcine respiratory coronavirus and the laboratory results suggested that the drug may effectively reduce the inflammatory response in the acute phase of infection (11). However, the results of the effectiveness of these drugs in different studies have been reported differently and have not yet been fully determined. The reason for this may be due to differences in the type and timing of medication. Due to this, we designed a trial to test a hypothesis that early administration of dexamethasone in combination with IV-IG and interferon-beta can reduce the effect of cytokine storm in the critically ill patient of COVID-19.

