**Methods for additional analyses (e.g. subgroup analyses) {20b}**

One of the researchers in our team will evaluate all data extracted from HIS and check the missing data. If possible, the subgroup analyses will be done based on the results.

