This trial has some limitations. This trial works on critically ill patients who have an inherently high mortality rate. This leads to loss to follow up and information or may affect the sample size. Secondly, due to the nature of the study, blinding is limited for some staff such as statisticians, and care providers cannot be blinded. Third, when we use allocation concealment using opaque envelopes, there is always a chance for subversion. Anyway, we will try to do fast this allocation to reduce the chance of subversion.

However, this trial is a multicenter RCT study and can provide more significant and useful data for the management of COVID-19. Generally, it is expected that this RCT show evidence that corticosteroids are effective in controlling cytokine storm and can use in the first stage of ARDS in critically ill COVID-19 cases.

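### The protocol names a two-group test for a three-arm trial, leaves the primary comparison open under one undivided 5%, and lets the results choose the subgroups

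*Protocol*

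**What the plan says.** - Trial design {8} sets three parallel arms, 1:1:1. Objective {7} asks about the efficacy of different ways of giving the combination, so the contrast between the two interventions is of interest as well as each against control.
- Outcomes {12} makes the primary outcome binary for each patient: SpO2 rises above 90% or it does not.
- Statistical methods {20a}: "The effect of outcomes between two interventions and the control groups will be assessed by chi-square" or Fisher's exact test for categorical data. Normally distributed data get the independent t-test. No order of comparisons is given.
- Sample size {14}: "assuming a two-sided 5% significance level and a power of 80%, 35 patients will be our sample size in each group". The effect is attributed to reference 10, but no rate, mean, SD or difference is given, and neither the endpoint nor the pair of arms is named.
- Background {6a} describes reference 10 as a study of methylprednisolone against a control group: "These cases had a faster improvement of SPO2 and shorter hospital stay days compared to the control group".
- Additional analyses {20b}: "If possible, the subgroup analyses will be done based on the results".

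**The concern.** An independent t-test cannot compare three groups at once, so continuous outcomes will be tested in pairs. For the primary outcome the wording allows a single 3x2 test, two comparisons with control, or all three pairs, and these have different error rates under the same nominal 5%. If the choice is made after the data are seen, the 5% no longer has a fixed meaning.

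The power statement has the same gap. It comes from a two-group steroid-versus-control study, described by speed of SpO2 improvement and length of stay. Nothing in it bears on intervention 1 against intervention 2, both of which contain dexamethasone. A reader could take 80% to cover every contrast.

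Subgroups chosen from the results cannot be given an error rate at all. Section {5d} says the findings will feed a new treatment algorithm, so a chance finding could carry weight.

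**Working it through.** **Inputs from the Protocol.** Three arms, 35 per arm, two-sided 5%, power 80% (sections {8} and {14}). **Assumptions.** Control response rates of 20-60%, because none is stated.

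**1. The plan's own figure.** The 35 cannot be reproduced, because no effect is given. Solving backwards for one two-group test:

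- Means: d = (z₀.₉₇₅ + z₀.₈₀) × √(2/n) = (1.960 + 0.842) × √(2/35) = 2.802 × 0.239 = 0.67 SD. With the t distribution it is 0.68 SD.
- Proportions (pooled normal approximation), difference needed for 80% power at 35 per arm:

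| Control rate (assumed) | Intervention rate needed | Difference |
|---|---|---|
| 20% | 51.6% | 31.6 points |
| 30% | 62.8% | 32.8 points |
| 40% | 72.7% | 32.7 points |
| 50% | 81.3% | 31.3 points |
| 60% | 88.7% | 28.7 points |

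So 35 per arm fits one unadjusted pair with a difference of about 31-33 points for control rates of 20-50%.

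**2. Chance of at least one false positive, one outcome, all arms equal, each test at 5%.**

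- One three-group test (2 df): 5% by design. Simulated Pearson chi-square at 35 per arm gives 5.0-5.2%.
- Two comparisons sharing the control: 1 − P(|Z₁| < 1.96 and |Z₂| < 1.96) with correlation 0.5 = 9.1%. Simulated chi-square gives 7.8-9.1%.
- All three pairs: P(studentized range of 3 groups, 102 df, exceeds √2 × t₀.₉₇₅) = 12.1%. Simulated chi-square gives 10.5-12.2%.

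The chi-square ranges come from varying the common response rate, and are lower in places because the test is discrete. Secondary outcomes, subgroups and the interim look are not counted.

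**3. Power for intervention 1 against 2.** Suppose that they differ by half the detectable effect: 0.67 / 2 = 0.335 SD. Then 0.335 / 0.239 = 1.40, and Φ(1.40 − 1.96) = Φ(−0.56) = 0.288, about 29%. The t calculation also gives 0.288.

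**4. What controlling the error costs at 35 per arm, same effect.**

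- Bonferroni at 2.5% (two tests): about 71% per comparison.
- Bonferroni at 1.67% (three tests): about 65%.
- Global test at 5%, then the pair at 5% (simulated for means): about 76% if the third arm equals either member of the pair, and 70% if it lies midway. For 50% against 81.3% with the third arm midway, also 70%. The probability of any false positive when all arms are equal is 5.0%.

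The last rule is a closed test with exactly three arms. Any two equal pairs imply that all three arms are equal, so the global test protects that case. If only one pair is equal, it is the only true null hypothesis and is tested at 5%.

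**The case against.** The strongest reply is that 12% belongs to one reading only. A chi-square or Fisher test applies to a 3x2 table, and the t-test does not touch a binary primary outcome. Section {20a} speaks of the two interventions and the control, and never says that the interventions will be tested against each other. This stands: it is why the size is given as a range starting at 5%. But a significant three-group test would not say which arm differs, and no rule for the next step is given.

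A reader might also infer that the 80% power is not delivered. The documents do not support that. Unadjusted tests at 5% keep 80% for each pair at the planned effect. Power falls only if the level is adjusted, so inflated error and this loss of power are alternatives. With the effect unstated, 35 per arm can be neither confirmed nor refuted.

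Nor does the admitted loss of information ("This leads to loss to follow up and information or may affect the sample size") give a figure for lost power. No loss rate is stated. Section {14} links the loss to mortality nowhere; the Discussion does, and under intention to treat a patient who dies without reaching the SpO2 threshold can count as a non-responder.

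Multiplicity rules and covariates are commonly left to an SAP, which is not shown, and an unadjusted chi-square is valid after randomization. Absence of an adjustment would therefore be no finding by itself. The t-test for three arms and the subgroup rule are stated in the Protocol, and an SAP could change them only by departing from it.

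**Conclusion.** The point holds in limited form. The Protocol prescribes a two-group test for continuous outcomes in a three-arm trial, leaves the primary comparison undefined under a single 5%, and states a results-driven rule for subgroups. The false-positive chance for one outcome is about 5%, 8-9% or 10-12%, depending on which comparisons are run. That 80% refers to one two-group comparison is an inference: a two-sided level fits a two-group test, and the cited source had two groups. On that inference, 35 per arm means about 0.68 SD or 31-33 points at assumed control rates of 20-50%. The 29% for intervention 1 against 2 rests on the assumption that they differ by half of that effect. It means that a non-significant result for this pair would say little about equal efficacy. The Protocol does not claim that it would.

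**What to change.** 1. **Section {20a}.** Test the primary outcome with a logistic model containing arm, baseline SpO2, age and sex, using a global 2-df test of arm at 5%. Test pairs at 5% each only if the global test is significant. Use ANOVA or ANCOVA in the same order for continuous outcomes. Intervention 1 against 2 is the third pair in this closed test. Always report its estimate with a confidence interval, so that a non-significant result is not taken as equal efficacy. The covariates are a gain in precision and are not needed for validity.
2. **Section {14}.** State the endpoint and the effect assumed. Say that 80% applies to one unadjusted two-arm comparison, and that power for that pair under the global-then-pair rule is about 70-76%, depending on the third arm. Any allowance for loss should be labelled as an assumption.
3. **Section {20b}.** Replace the results-based rule by named baseline subgroups (baseline SpO2, age, sex), tested by interaction and labelled exploratory.

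**Cost.** Wording only, to be settled before the data are unblinded. Nominal power for one pair falls by 4 points (80 − 76) to 10 points (80 − 70), and the stated figure is less favourable. Adjusting for baseline SpO2 may recover part of this. Bonferroni would cost more in most cases: 9 points for two tests (80 − 71) or 15 for three (80 − 65).

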**Eligibility criteria {10}**

The following eligibility criteria will be set for participants:

Inclusion criteria: age 18-70 years old; proven of severe COVID-19 cases.

Exclusion criteria: the need for intubation; allergy, intolerance, or contraindication to any study drug including dexamethasone, IV-IG, and interferon-beta; pregnancy or lactation; known HIV positivity or active hepatitis B or C.

A critically ill COVID-19 case is defined as a patient with positive RT-PCR test who have a blood oxygen saturation level (SpO2) less than 90% and respiratory rate higher than 24 per minute or have involvement of more than 50% of his/her lung when viewed using computed tomography (CT)-scan. Internal medicine, pulmonologist, and nurses will perform the interventions.

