**Intervention description {11a}**

The study subjects will be randomly allocated in three treatment arms and divided into two experimental groups (two arms: intervention 1 and intervention 2) and one control group, which will be matched for age and sex using frequency matching method (Figure 1). Each eligible patient in the control arm will be received the standard treatment for COVID-19 (a combination of antiviral drugs) and the usual standard of care according to the protocol of MOHME of Iran. If the proposed standard treatment is changed, all patients will receive a new suggestion for further treatment. Each patient in the intervention 1 group will receive the standard treatment for COVID-19 and dexamethasone, (as described below), during the first 24 hours of admission. The dexamethasone will be administrated base on the level of SpO2. If the level of SpO2 does not improve after 24 hours, IV-IG and interferon-beta will be prescribed as shown below along with dexamethasone administration. In the intervention 2 group, the administration of dexamethasone will be started at the first 24 hours of admission and will be continued until 48-72 hours and the level of SpO2 will be checked. Then, if the level of SpO2 does not improve after that time, IV-IG and interferon-beta will be prescribed as the same.

Drug dosages and duration of the regimes are stated below for each intervention group. The intervention begins with the administration of dexamethasone:

If the percentage of the SpO2 level is between 85 and 90, the dosage will be 4 mg every 12 h,

If the percentage of the SpO2 level is between 80 and 85, the dosage will be 4 mg every 8 h,

If the percentage of the SpO2 level is between 75 and 80, the dosage will be 8 mg every 12 h,

If the percentage of the SpO2 level is less than 75, the dosage will be 8 mg every 8 h.

The doses of IV-IG will be 400 mg/kg once daily for 5 days and interferon-beta will be 7 doses every other day. As a note, before the IV-IG administration, the level of IgA will be checked.

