**Outcomes {12}**

**Primary outcome**

An increase in the SpO2 level to reach more than 90% in each case, which will be assessed by the oximeter.

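### The binary primary outcome is to be tested without adjustment for entry SpO2, which is already measured; the test is valid, but a prespecified adjusted analysis would probably gain some power and correct for chance imbalance

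*Protocol*

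**What the plan says.** The Protocol defines the primary outcome as "An increase in the SpO2 level to reach more than 90% in each case, which will be assessed by the oximeter". That is a yes/no result per patient. For such outcomes, section {20a} states: "The effect of outcomes between two interventions and the control groups will be assessed by chi-square", and the same sentence gives Fisher's exact test as the alternative. It names no covariate, and section {20b} adds only unspecified subgroup analyses.

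Entry SpO2 appears in three other places:

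- **Eligibility {10}:** it is part of the case definition, "blood oxygen saturation level (SpO2) less than 90% and respiratory rate higher than 24 per minute or have involvement of more than 50" percent of the lung on CT.
- **Intervention description {11a}:** it selects one of four dosing bands, from 85–90 down to the lowest: "If the percentage of the SpO2 level is less than 75, the dosage will be 8 mg every 8 h".
- **Plans for assessment and collection of outcomes {18a}:** "The level of SpO2 (the primary outcome) will be daily measured by oximeter".

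Allocation is by simple randomisation, 1:1:1, with 35 per arm (sections {14} and {16a}). The only balancing factors named are in section {11a}, which says that the groups will be "matched for age and sex using frequency matching method". Entry SpO2 is not among them.

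**The concern.** A patient who enters at 89% has a short way to go to pass 90%; one who enters at 74% has more than 15 points. The bands show that the protocol provides for both. If this distance affects who responds, an analysis that ignores it has two costs.

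The first is power: variation that a baseline value could explain stays in the comparison. The second is chance imbalance. With 35 per arm and no stratification, an intervention arm can start with clearly better or worse saturation than control, and an unadjusted test counts that difference as part of the treatment effect. With only 105 patients and a nominal power of 80%, neither cost is trivial, and the data needed to avoid both are collected anyway.

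**Working it through.** **1. The plan's own figure.** Section {14} gives 35 per arm, "assuming a two-sided 5% significance level and a power of 80" percent, but no response rates or effect size. The figure therefore cannot be reproduced forwards. Solved backwards, the standardised difference is (1.960 + 0.842) × √(2/35) = 0.67. For proportions without continuity correction, 35 per arm fits about 30% v 63%, 40% v 73%, 50% v 81.5% or 60% v 89%. For 40% v 73%, the mean rate is 0.565 and

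n = [1.960 × √(2 × 0.565 × 0.435) + 0.842 × √(0.4 × 0.6 + 0.73 × 0.27)]² / 0.33² = (1.374 + 0.556)² / 0.1089 ≈ 34.2, so 35.

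The sample size is neither confirmed nor shown wrong. Every power figure below is a scenario.

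**2. Power, treatment odds ratio held fixed.** Assumed: one intervention arm v control, 35 each; control response 50%; treatment odds ratio 5 at a given entry SpO2; entry SpO2 normal. Pearson chi-square is compared by simulation with a logistic likelihood-ratio test that has arm and entry SpO2 only.

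| Odds ratio per SD of entry SpO2 | Unadjusted | Adjusted, nominal cutoff | Gain with both tests at true 5% size |
|---|---|---|---|
| 1.8 | 82% | 85% | about 1 point |
| 2.7 | 76% | 83% | about 4 points |
| 4.1 | 65% | 78% | about 10 points |

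The last column is the fair comparison. Under the null the adjusted test rejected in 5.2–5.8% of trials, while chi-square runs below 5% (step 4), so the nominal columns flatter adjustment.

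**3. Power, response rates held fixed at 40% v 73%.** At nominal cutoffs, unadjusted to adjusted:

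- odds ratio 1 per SD: 80% to 81% (no material gain)
- 1.5: 80% to 83%
- 2: 79% to 85%
- 3: 79% to 89%
- 5: 80% to 92%

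These are not size-corrected, so they are upper readings. The direction agrees with step 2.

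**4. Validity and imbalance.** Under the null (50% v 50%) chi-square rejected in 4.1–4.5% of trials, so its overall type I error is kept. In the roughly 5% of trials where the arms differ by more than 0.48 SD in mean entry SpO2 (2 standard errors: 2 × √(2/35) = 0.48), chi-square rejected in 8%, 14% and 20% at odds ratios of 2, 3 and 5 per SD. The adjusted test stayed at 4–6%.

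**5. How often imbalance occurs.** The standard error of a difference in means is SD × √(2/35). With an assumed SD of 4 points it is 0.96, and a difference of 2 points or more has probability 2 × [1 − Φ(2/0.96)] ≈ 4%. With SD 6 it is 1.43, and the probability is about 16%. These are for one comparison; the trial has two intervention arms.

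**6. A larger model.** With three arms, age, sex and five hospitals (an assumed number, all these extra terms non-prognostic), the likelihood-ratio test rejected 6.1–6.8% under the null. At true 5% size its gain over chi-square was about −3, +2 and +6 points at the three odds ratios of step 2. The extra terms can erase the benefit of adjustment.

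**The case against.** The strongest reply is that nothing here is an error. A chi-square test of a randomised binary outcome is valid, covariate lists often sit in a statistical analysis plan, and none is at hand. The first part stands: this is a matter of efficiency and of protection against imbalance. The second stands in part. Section {20a} does more than leave the method open, since it names the tests for the primary outcome. If an analysis plan already adds adjustment for entry SpO2, the point is met and only the protocol wording needs aligning.

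A reader might infer that entry SpO2 largely determines who passes 90%. The Protocol does not say so. The bands are dosing rules and do not describe the entry distribution. The primary outcome section gives no time point, so the strength of prediction cannot be judged from the text. Dose and added drugs also depend on SpO2, so the treatment effect may vary with the entry value, whereas step 2 assumes one constant odds ratio.

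A reader might also infer that the unadjusted result is biased or has an inflated error rate. Over all randomisations it does not; the excess in step 4 is conditional on an unlucky allocation.

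Finally, a reader might want every available baseline factor in the model. Step 6 speaks against that: the number of hospitals is not stated, and sparse terms raise the false-positive rate.

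**Conclusion.** The concern holds as an inexpensive improvement to a valid analysis. The Protocol fixes an unadjusted test, and neither design nor analysis uses the baseline value of the primary endpoint, although it is available for every patient. Under the step 2 assumptions the benefit of adjustment is about 1, 4 and 10 points of power at true 5% size for odds ratios of 1.8, 2.7 and 4.1 per SD, and none if entry SpO2 is not prognostic. Protection against chance imbalance comes in addition. That entry SpO2 is prognostic is likely, because it is the same measurement taken earlier, but its strength is an assumption. The loss for this particular trial cannot be stated, because no response rates are given.

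**What to change.** In section {20a}, prespecify as the primary analysis a logistic model with arm and entry SpO2 as a continuous covariate, and state which reading counts as the entry value. Report odds ratios and standardised risk differences for each intervention arm versus control. Keep the chi-square or Fisher's exact result as the supporting unadjusted analysis.

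Age and sex may be added, since section {11a} names them as balancing factors. Hospital terms should not be required.

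The cost is wording only; no new data are needed. There are two downsides. The covariates must be fixed before unblinding. The likelihood-ratio test is also slightly liberal at this size (about 5–6%), so a small-sample or penalised version may be preferred.
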